## Abstract

**Background:**

Chronic obstructive pulmonary disease (COPD) has become a major public health problem worldwide because of its high and increasing prevalence, morbidity, and mortality. Little attention has been paid to earlier stages of COPD or before it has developed. Reportedly, TCM may have some advantages in relieving symptoms and reducing the incidence of COPD exacerbations. We postulate that patients with COPD will benefit from therapy with TCM treatment according to syndrome differentiation.

**Methods and design:**

A prospective, multi-center, double-blinded and randomized controlled method will be used to test the therapeutic effects of TCM treatment according to syndrome differentiation. A total of 504 patients will be enrolled into this study with 252 in each treatment group. Patients will receive medication according to their assigned group. TCM for COPD will be administered twice daily over 52 weeks, and all patients will follow the treatment program for 52 weeks. The FEV_1_ and exacerbations will be used as the primary outcome measures. The quality of life and the Modified Medical Research Council (MMRC) Dyspnea Scale, and the 6-min walk test (6MWD) will be used as the secondary outcome measures.

**Discussion:**

We postulate that patients with COPD will benefit from therapy with TCM treatment according to syndrome differentiation.

**Trial registration:**

This study is registered at ClinicalTrials.gov, NCT01486186

## Background

Chronic obstructive pulmonary disease (COPD) has become a major public health problem worldwide because of its high and increasing prevalence, morbidity and mortality [1,2]. A recent report estimated that the global prevalence of COPD (stage II or over) is about 10% (12% in men and 9% in women) [3]. In China, COPD affects 8% of the population aged 40 and above [4], and is one of the top diseases in the World Health Organization’s ranking of burden of diseases [5]. It is therefore necessary to develop a reliable intervention strategy for the prevention and management of COPD to reduce the burden of this disease.

Current interventions for COPD (such as smoking cessation, rehabilitation, nutrition support, drug treatments and psychosocial aids) are mainly on a case-by-case basis among patients who have already developed moderately or severely symptomatic COPD, while little attention has been paid to earlier stages of the disease or before it has developed. Although there has been some progress with case-based or hospital-based interventions [such as improvements in exercise capacity, forced expiratory volume in 1 s (FEV_1_) and health-related quality of life, fewer hospital admissions and acute exacerbations, and lower all-cause mortality] [6-9], such efforts for the prevention of COPD are limited among the general population in China. Few patients are diagnosed until they develop severe symptoms and signs, and pulmonary function tests are not routinely performed.

Traditional Chinese medicine (TCM) is very popularly used for COPD in Asia, and reportedly TCM may have some advantages in relieving symptoms, reducing the incidence of COPD exacerbations and improving the quality of life for COPD patients [10,11].

We report in this article on a multi-center, randomized, double-blinded, placebo-controlled trial of traditional Chinese medicine treatment with syndrome differentiation to test the hypothesis that patients with COPD will benefit from the therapy with TCM.

### Objective

To determine whether treatment with TCM with syndrome differentiation reduces exacerbation frequency.

## Methods and design

### Study design

This clinical trial has a multi-centered, randomized, double-blinded, placebo-controlled design. The study design will integrate rigorous, contemporary clinical research methodology in accord with the principles set out in the Declaration of Helsinki and the Good Clinical Practice guidelines according to the theory that guides the appropriate use of TCM in clinical practice. Reporting will be guided by the CONSORT statement [12,13]. Subjects will be enrolled at 12 hospitals: (1) the First Affiliated Hospital of Henan University of TCM, (2) TCM Hospital of Xinjiang Uygur Autonomous Region; (3) the First Affiliated Hospital of Anhui University of TCM; (4) Xiyuan Hospital of the China Academy of Chinese Medical Sciences; (5) Jiangsu Province Hospital of TCM; (6) Shanghai Shuguang Hospital affiliated with Shanghai University of Traditional Chinese Medicine; (7) the Second Affiliated Hospital of Guiyang College of TCM; (8) Jilin Academy of Traditional Chinese Medicine; (9) Shanxi Sheng Zhongyi Hospital; (10) the First Teaching Hospital of Tianjing University of TCM; (11) the First Affiliated Hospital of Guangzhou University of TCM; (12) Jiangxi Province Hospital of TCM. This study will be conducted at 12 sites in China. Twelve hospitals in China will randomly assign 504 patients with COPD at a ratio of 1:1 into the TCM treatment or matching placebo group. Consenting eligible participants will be enrolled for 2 weeks and will be required to attend seven visits in total. The trial is designed in two phases, 52 weeks of treatment with either TCM for COPD or placebo granules, and 52 weeks of follow-up.

### Study duration

Ongoing recruitment will occur for a maximum period of 18 months (between July 2011 and December 2013) or until a sample of 504 individuals has been randomized.

### Subjects

A total of 504 participants will be recruited through local advertising and doctor referrals from hospital outpatients and general practice clinics. Interested participants can telephone or email the trial coordinators at the corresponding sites for further information. Participant information and consent forms will be sent to interested individuals to read over prior to scheduling their first visit.

### Inclusion criteria for participation in the trial

The inclusion criteria are as follows: (1) a confirmed diagnosis of mild/moderate COPD; (2) males and females aged between 40 and 80 years; (3) meeting the TCM diagnostic criteria (syndrome differentiation includes lung *qi* deficiency, pulmonosplenic *qi* deficiency and insufficient lung and kidney *qi* syndromes); (4) not having participated in other interventional trials in the previous 1 month; (5) giving written informed consent to participate.

### Exclusion criteria

Exclusion criteria include: (1) pregnant or breast-feeding women; (2) any psychiatric condition rendering the patient unable to understand the nature, scope and possible consequences of the study; (3) complication of severe heart failure (NYHA heart function class IV) or unstable hemodynamics; (4) complication of bronchial asthma, bronchiectasis or active tuberculosis, obliterative bronchiolitis or diffuse pantothenic bronchiolitis, pneumothorax, pleural effusion or pulmonary embolism; (5) complication of neuromuscular disorders affecting respiration or of tumors; (6) complication of serious hepatic and renal diseases; (7) long periods of bed rest; (8) use of oral or parenteral corticosteroids in the 1 month before the first visit; (9) having immunodeficiency; (10) participating in other trials or being allergic to the used medicine.

This study is to be conducted in accordance with patient protection as outlined in the Declaration of Helsinki and approved by the appropriate Institutional Review Boards. Each participant will sign the written informed consent form before undergoing any examinations or study procedures, in compliance with Good Clinical Practice. Patients who initially meet the eligibility criteria are then to complete the additional baseline testing and will be randomized into either the treatment or control group.

### Ethics issues

This study has been approved by the Ethics Committee of the First Affiliated Hospital of Henan University of TCM (no: 2011HL-034). Each participating center obtained local institutional review board approval. All study participants will sign the written informed consent prior to participation.

### Interventions

Eligible patients will be randomized to one of the two arms: receiving a placebo or a Chinese medical herb. An herbal extract will be given twice daily for 52 weeks. There are three recipes for the three traditional Chinese syndromes: lung *qi* deficiency, pulmonosplenic *qi* deficiency, and lung and kidney *qi* insufficiency syndromes. The experimental group will receive three types of TCM: Baofei granules, Bufeijianpi granules and Bufeiyishen granules. The placebo comparison group will receive placebo Chinese medicine in addition to best care according to the clinical guidelines for COPD patients.

Randomization of subjects will occur centrally using a random number generator and will be stratified by syndrome differentiation of TCM (a syndrome, as related to illnesses in Western medicine, is composed of a set of signs and/or symptoms classified by Traditional Chinese Medicine practitioners. TCM syndrome differentiation is based on symptoms and helps to identify a disease subset).

### Randomization and allocation

Treatment allocation occurs when the study participant meets the inclusion criteria and signs the informed consent form. The teletherapist will then register the participant into the database, which in turn asks if they are ready to be randomized. After the teletherapist enters “yes,” the site-specific randomization program behind the form displays the participant's group assignment number (placebo versus Chinese medical herb). Site-specific randomization lists will be computer-generated (i.e., generated by an individualized basic visual code program) and concealed from the researchers by a senior data manager who is not involved in the study. This information will remain confidential and will not be shared with the study sites, in concordance with the CONSORT guidelines. This trial uses a prospective, randomized, double-blinded design. The allocation list will be protected by password access files and held by an independent non-investigator. In the event of an emergency medical situation, the individual’s randomization code and group allocation can be identified.

### Sample size

The sample size calculation is based on the annual decline of mean forced expiratory volume in 1 s (FEV_1_) in COPD subjects. The previous study showed that the mean rate of change in FEV_1_ was a decline of 51 ml per year in patients with TCM treatment and 131 ml per year in patients with usual care with mild/moderate COPD. According to the sample size of the estimation formula $n=2{\left[\frac{(u_{a}+u_{\varphi })\sigma }{\delta }\right]}^{2}$, n1 = n2 = 2(1.64 + 1.28)^2^ × 0.28^2^/0.08^2^ = 209. It is estimated that a sample size of 209 subjects per group will be required, considering 20% drop out and exit. This results in 504 in total. Intention-to-treat analysis will be applied to minimize bias due to drop-outs.

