### Statistical analysis

Descriptive statistical analysis will be performed for all the study variables. We will calculate the mean, median and standard deviations for quantitative variables, and the absolute and relative frequency for qualitative variables.

We use SPSS 19.0 (license no.: 6f1d84c801f1e6010dc, SPSS Inc., Chicago, IL, USA) to statistically analyze the data. An intention-to-treat analysis will be applied using the Last Observation Carried Forward (LOCF) method. Analysis of covariance with baseline as covariate will be used to assess differences in treatment outcomes between the two groups at each of these time points. To correct for inflated risk of type 1 error, multiple comparison procedures suggested by Ludbrook et al. will be used [16]. The use of relief medication during the trial will be investigated for its effect on the outcome measures by using it as a covariate in the statistical analysis. A Data Safety Monitoring Board has been established to assess the progress of the trial, particularly safety endpoints.

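### The sample size rests on an undeclared one-sided 5% level; at two-sided 5% the 209 per arm gives about 83% power, not the implied 90%

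*Protocol article*

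**What the plan says.** The Sample size section bases the calculation on the annual change in FEV1, citing "a decline of 51 ml per year in patients with TCM treatment and 131 ml per year in patients with usual care", which is a difference of 80 ml per year. It applies the standard two-sample formula: "n1 = n2 = 2(1.64 + 1.28)^2^ × 0.28^2^/0.08^2^ = 209". The SD of 0.28 L appears only inside that formula. Alpha, sidedness and power are not given in words anywhere in the article.

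The same section then says that "a sample size of 209 subjects per group will be required, considering 20% drop out and exit", leading to 504 in total. The Abstract confirms this: "A total of 504 patients will be enrolled into this study with 252 in each treatment group".

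The Statistical analysis section gives the test: "Analysis of covariance with baseline as covariate will be used to assess differences in treatment outcomes between the two groups". It adds intention-to-treat with last observation carried forward (LOCF), and a multiple comparison procedure to control type 1 error. It names no one-sided test and no 10% two-sided level.

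**The concern.** The calculation takes its critical value from a one-sided 5% test. The analysis section describes a comparison for a difference between groups by analysis of covariance, and the usual F or t test of the group term in that model is two-sided. If the analysis is run at the conventional two-sided 5%, the planning level was twice as generous as the level applied to the data, and the power built into the formula is not delivered.

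This is the trial's only sample size justification. A non-significant FEV1 result could be judged against a type 2 error of 10% when the real figure is higher. If sidedness stays open until the data are in, a one-sided p-value reported later would look selective. The article reports 150 patients recruited at submission, so the level can still be settled well before results.

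**Working it through.** **Inputs, all from the Sample size section unless noted**
- Critical value for alpha: 1.64
- Quantile for power: 1.28 (90%)
- Difference: 131 − 51 = 80 ml per year = 0.08 L
- SD: 0.28 L
- Drop-out: 20%
- Enrolled: 252 per arm (Abstract), allocated 1:1 (Study design)
- Assumed, not stated: two-sided 5%, critical value 1.96

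**Step 1. Reproduce the plan's figure.** The formula is n = 2[(z_α + z_β)σ/δ]². Here 0.28²/0.08² = 12.25, so n = 2 × (1.64 + 1.28)² × 12.25 = 2 × 8.5264 × 12.25 = 208.9, which rounds to 209. The arithmetic is correct as printed.

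**Step 2. See whether a two-sided 5% reading could also give 209.** With the same difference and SD, per arm:

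| Level | Power | n per arm |
|---|---|---|
| Two-sided 5% | 80% | 193 |
| Two-sided 5% | 85% | 220 |
| Two-sided 5% | 90% | 258 |
| One-sided 5% (= two-sided 10%) | 90% | 210 (209 with the rounded quantiles) |

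Of these, only the last row matches. The 90% row at two-sided 5% is 2 × (1.96 + 1.28)² × 12.25 = 257.2, so 258.

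**Step 3. Power at two-sided 5%.** Power = Φ(δ/(σ√(2/n)) − 1.96).
- n = 209: 0.08/(0.28 × √(2/209)) = 2.921; 2.921 − 1.96 = 0.961; power 83.2%. A noncentral t calculation gives 83.0%. At one-sided 5% the same n gives 89.9%.
- n = 201 (252 × 0.8 = 201.6, rounded down): 2.864 − 1.96 = 0.904; power 81.7%.
- n = 252: 3.207 − 1.96 = 1.247; power 89.4%.

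The 258 evaluable patients needed for 90% exceed the 252 enrolled, so even complete retention falls slightly short.

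**Step 4. How far the result depends on drop-out handling.** LOCF keeps drop-outs in the analysis, but their carried-forward values may shrink the difference. As an illustration only, suppose 20% of patients contribute no treatment effect and the SD is unchanged. The difference becomes 0.8 × 80 = 64 ml. At 252 per arm, 0.064/(0.28 × √(2/252)) = 2.566; 2.566 − 1.96 = 0.606; power is about 73%.

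**Step 5. Multiplicity, as an illustration only.** The article lists two primary outcomes. If alpha were split equally (two-sided 2.5%, critical value 2.241), power would be about 75% at 209 per arm (2.921 − 2.241 = 0.680) and about 73% at 201 (2.864 − 2.241 = 0.623).

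**The case against.** The strongest reply is that no analysis alpha exists to contradict. Wording about assessing differences is routine, and a treatment contrast from an analysis of covariance can be tested one-sided. The stated hypothesis and objective are directional (benefit from therapy, fewer exacerbations). Test level and sidedness are often left to a full protocol or analysis plan, neither of which is shown. This stands in part: a reader might infer a proven factor-of-two conflict between two stated levels, and the article does not support that. However, the point does not rest on silence. The article itself fixes 1.64. A directional hope is normal in a superiority trial and does not define a one-sided test, and the stated objective concerns exacerbations, not the FEV1 endpoint used for sizing.

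The second reply is that neither 83% nor 82% is the power of the planned analysis. Intention-to-treat with LOCF aims to include all 252 per arm, where power is 89.4%, close to the implied 90%. This stands. The 201 per arm describes completers, whom the plan does not single out, and the 89.4% assumes that drop-outs carry the full effect. A range is therefore the honest statement.

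Third, baseline adjustment may gain precision. It may, but the article gives no correlation and does not say whether 0.28 L is already the SD of annual change, so the gain cannot be quantified.

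Finally, the article never states 90% in words; it follows only from 1.28.

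**Conclusion.** The point holds as an undeclared one-sided planning level. Conditional on a two-sided 5% test, a difference of 80 ml per year and an SD of 280 ml, the 209 per arm gives about 83% power, not the 90% implied. For the 504 actually planned, power runs from about 82% (about 201 per arm contributing) up to about 89% (all 252 per arm, no dilution). It is lower if carried-forward values dilute the effect. All of these are before any multiplicity correction.

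Three stronger readings are tempting and should be resisted. It is not an arithmetic slip, since 208.9 rounds to the printed 209. It is not an established contradiction between two declared alphas, since the article declares none. It does not show that the trial needs more patients, because without dilution or multiplicity correction power for the assumed difference stays above 80%. Estimates, randomisation and conduct are unaffected. It should be fixed, but it is not critical.

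**What to change.** In Sample size and in Statistical analysis, state that tests are at two-sided 5% with 95% confidence intervals. Replace the implied 90% with the range above for 504 randomised, naming the difference, the SD, the drop-out handling behind each end of the range, and the fact that no multiplicity correction is included. If the sponsor really intends a one-sided 5% test, both sections must declare and justify it, since that is twice the usual one-sided error of 2.5%.

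The cost is a few sentences and a less favourable stated power. No extra patients and no change to conduct are needed. Keeping 90% at two-sided 5% after 20% loss would instead take 258/0.8 = 322.5, so 323 per arm or 646 in total, which this point does not call for.

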#### Adverse event reporting

pirometry at each site will be conducted using SpiroUSB™ (CareFusion) and Spida5® software. Routine calibration and standard operating procedures will be uniformly undertaken at each site. Participants will be advised not to use respiratory medications for several hours prior to their spirometry testing. Two sets of measurements will be taken at each visit, pre-bronchodilator and post-bronchodilator (post 400 μg of inhaled salbutamol).

Any adverse events will be listed in the trial record and followed up to completion by the trial coordinators and respiratory physicians. Adverse event details will be scored using a six-point scale: 0 = none, 1 = minimal, 2 = mild, 3 = moderate, 4 = severe and 5 = extremely severe. Participants will be able to report adverse events anytime throughout the trial and will receive advice accordingly. Serious adverse events will be reported to the reviewing Human Research Ethics Committee (HREC) and site HRECs within the timeframe specified by the lead HREC.

Throughout the study period, trial coordinators will contact the participant’s usual treating doctor to record relevant data on presentations and exacerbations.

To assist with outcome documentation and medication compliance, participants will be given a participant diary for the duration of the trial. They will be asked to record trial medication and relief medication usage as well as any new medications they commence during the trial.

Participants may withdraw from the study for any reason at any time without repercussions. They will only be withdrawn by investigators if it is deemed medically unsafe for them to continue. Dropouts will not be replaced.

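### The 20% drop-out allowance is not met: 252 per arm leaves about 201 completers, below the 209 the plan requires, because 209 appears to have been multiplied by about 1.2 instead of divided by 0.8.

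*Protocol article*

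**What the plan says.** The Sample size section takes its effect from an earlier study, which reported "a decline of 51 ml per year in patients with TCM treatment and 131 ml per year in patients with usual care". It prints the calculation as "n1 = n2 = 2(1.64 + 1.28)^2^ × 0.28^2^/0.08^2^ = 209". The next sentence reads "It is estimated that a sample size of 209 subjects per group will be required, considering 20% drop out and exit", and the one after it "This results in 504 in total". The step from 209 per group to 504 is not shown.

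The abstract gives the split: "A total of 504 patients will be enrolled into this study with 252 in each treatment group". The Study design section confirms 1:1 allocation of the 504. The text on withdrawals, under Adverse event reporting, adds "Dropouts will not be replaced". The Sample size and Statistical analysis sections plan an intention-to-treat analysis, the latter using last observation carried forward (LOCF).

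**The concern.** A drop-out rate is a share of the patients randomised. To have n patients left after a fraction d is lost, n/(1 − d) must be randomised. Multiplying n by (1 + d) gives a smaller number and falls short whenever d is above zero. The figure of 252 per arm is close to 209 × 1.2 and clearly below 209/0.8, so the allowance seems to have been applied the wrong way.

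If so, the published justification claims a margin the trial does not have. At the plan's own drop-out rate, the number with complete data falls below the number the plan calls necessary, and the rule against replacement means nothing makes up the gap.

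**Working it through.** **Inputs, from the Sample size section unless noted**

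- Difference in annual FEV1 decline: 131 − 51 = 80 ml = 0.08 L.
- Standard deviation: 0.28 L.
- Normal quantiles: 1.64 and 1.28. These correspond to one-sided 5% and 90% power, neither of which is stated in words.
- Drop-out: 20%.
- Randomised: 504, or 252 per arm (Abstract).
- Replacement: none (Adverse event reporting).

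**1. The plan's figure before losses**

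n = 2 × (1.64 + 1.28)² × 0.28² / 0.08² = 208.9, rounded up to 209 per arm. This reproduces. With unrounded quantiles the result is 210. The formula contains no drop-out term.

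**2. How 252 could have been reached**

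| Route | Per arm | Total |
|---|---|---|
| 209 × 1.2 | 250.8, so 251 | 502 |
| 210 × 1.2 | 252 | 504 |
| 209 / 0.8 | 261.25, so 262 | 524 |
| Plan | 252 | 504 |

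Multiplication by 1.2 gives the plan's figure exactly from 210 and within one patient per arm from 209. Division by 0.8 does not: it gives 10 more per arm and 20 more in total, and 20/504 = 4.0%.

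**3. What 252 per arm delivers**

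- Left after 20% loss: 252 × 0.8 = 201.6, so 201 to 202 per arm. The shortfall against 209 is 7 to 8.
- Loss at which 209 still remain: 1 − 209/252 = 0.171, or 17.1%.

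**4. Effect on power**

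Power is Φ( (0.08/0.28) × √(n/2) − z ), with z = 1.645 for one-sided 5% and z = 1.960 for two-sided 5%.

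| Patients per arm | One-sided 5% (plan's basis) | Two-sided 5% |
|---|---|---|
| 209 | 89.9% | 83.2% |
| 201 | 88.9% | 81.7% |

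For example, with n = 201 on the plan's basis: 0.2857 × √100.5 = 2.864; 2.864 − 1.645 = 1.219; Φ(1.219) = 0.889.

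The two-sided column only shows that the loss stays small on the other common basis. The choice of a one-sided quantile is a separate matter.

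**The case against.** The best objection is that completers are not the planned analysis set. Under intention-to-treat with LOCF, a patient who leaves after week 26 still contributes a value, so the number analysed lies between about 201 and 252 per arm. This stands in part: the shortfall is in completers, not in patients analysed, and 88.9% is the power of a comparison among completers. But the trial is sized on a full year's change in FEV1, and on treatment FEV1 is measured only before treatment and at weeks 26 and 52. A patient lost before week 26 carries forward the baseline value, and one lost later carries a half-year value. Neither supplies an observed full-year change. The plan also added a drop-out allowance, so it treats losses as costing information.

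A second objection is that the multiplication is inferred, and that the plan never says in so many words that 209 will remain. The inference is fair to flag: from 209 the product is 250.8, and exactly 252 needs a start from 210, which the article does not print. The conclusion does not depend on it, because 80% of 252 is below 209 however 252 was reached. Reading 209 as already including losses also fails, since the formula has no such term and 2 × 209 = 418, not 504. If 20% was meant as an add-on to 209, it protects against a loss of only 1 − 1/1.2 = 16.7%.

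A third objection is that the gap lies within the precision of the inputs. A standard deviation of 0.275, which also rounds to 0.28, gives 2 × 2.92² × 0.275² / 0.08² = 201.5 per arm. The planned covariance analysis on baseline could also close the gap: with an assumed baseline–outcome correlation of 0.2, the required number falls by 0.2² = 4%, to about 201. Both points are correct and show how small the matter is. The plan's calculation claims neither, so they do not make its sentence true.

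**Conclusion.** The concern holds. On the plan's own inputs, 504 randomised does not retain 209 per group after 20% drop-out. It leaves about 201, and it retains 209 only if losses stay at or below about 17%. The total is 20 patients, about 4%, below what those inputs require.

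The consequence is modest: about one percentage point of power on the plan's one-sided basis (89.9% to 88.9%), or 1.5 points at two-sided 5% (83.2% to 81.7%). These figures assume equal loss in both arms, loss unrelated to outcome, and a comparison of patients with an observed full-year FEV1 change. The trial's validity is not in question. The error is in the stated justification for the sample size, which a reader can disprove in one line.

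**What to change.** Keep 504 and correct the Sample size sentence in one of two ways:

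- State that 209 per group is the requirement before losses, and that randomising 504 retains this number with up to 17% drop-out.
- Keep the 20% assumption, state that it leaves about 201 per group, and restate the power for that number: about 88.9% on the plan's one-sided basis, described as power among completers.

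Either version should print the step from 209 to 252. The second should also say that the LOCF analysis will include more patients than the completers.

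The cost is one sentence and a slightly less favourable figure. The design, recruitment target and analysis do not change. Enlarging the trial to 524 would also meet the claim, but a difference of about one point of power does not call for it.
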